#### Selection of health care workers

Ninety health care providers who give informed consent to participate in the study and meet the requirement of the selection criteria will be interviewed through a questionnaire to determine their knowledge and skills levels in neonatal care. The health care providers have already been trained in their respective areas but may be deficient in neonatal care. It is approximated that their knowledge on neonatology is at 65% and this needs to be increased up to about 90%. See Additional file 3.

#### Participants for in-depth interviews

In- depth interviews will be conducted with key informants in the selected project sites (See Additional file 4). They include the following:

1 – County Director of health services

1 – Director of nursing services in the county

1 – County RH coordinator

1 –Pediatrician in the county

9 – Medical Superintendents/Facility –in- charges – one in each Hospital

9- Nurses in – charge on maternity – one in each Facility

9- Staff in- charge of new born units

## 9 – In- charge of PNC services

### Limitation of sampling technique selected

The simple random sampling technique that will be employed in this study will require a lot of time to implement and is quite tedious. This implies that more resources shall be needed for the study and the implementing team will have to be robust enough to withstand the rigorous exercise.

### Quantitative data

Questionnaires –
i.This will be administered to health workers to check their knowledge, attitudes and practices in neonatal care.ii.Community (mothers of newborns/caregivers) to assess effect of information on their knowledge of danger signs and utilization of neonatal services.
Check list – Will consist of a list of equipment available in the new born care unit, their condition, and frequency of useData abstraction form –This will be developed to collect routine health facility records in the neonatal unit to ensure completeness and accuracy in data generated. The trained nurses and clinical officers will ensure correct data entry which will be monitored periodically by the hospital facility in conjunction with the project. The trained staff will also mentor other staff in the facility (OJT) to also develop competency and correct data recording and entry.Client exit interviews –will be administered to clients from new born unit to capture the perception of clients on quality of care provided, and the outcome of the service.

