## Abstract

**Background:**

Neonatal mortality is a major health burden in Bungoma County with the rate estimated at 31 per 1000 live births and is above the national average of 22 per 1000. Nonetheless, out of the nine sub county hospitals, only two are fairly equipped with necessary infrastructure and skilled personnel to manage neonatal complications such as prematurity, neonatal sepsis, neonatal jaundice, birth asphyxia and respiratory distress syndrome. Additionally, with more than 50% of neonates delivered without skilled attendance, in below par hygiene environments such as home and on the roadsides, with non-existent community based referral system, the situation is made worse. The study aims to evaluate the progress made by an intervention “Collaborative Newborn Support Project” geared towards reducing neonatal mortality rate by 30% between October 2015 and December 2018 in Bungoma County, Kenya.

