### Primary outcome measure

Percentage reduction in newborn deaths in Bungoma County between October 2015 and December 2018. This will be measured by comparing the number of newborn deaths at the nine project facilities (in the period of implementation), with the number of deaths at the same facilities in the similar period before the intervention; converted to percentage and aggregated by facility.

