### Control group – Minimizing bias and contamination

To minimize bias and contamination, the intervention sites will be selected purposely from the nine county and sub- county hospitals. The sites selected will include the two facilities that have some level of neonatal facilities to ensure that the intervention sites and the control sites have distinct features separating the two.

We will measure the utilization of services in the selected facilities at baseline, mid-term and end-line levels.

To determine utilization of neonatal services, we will collect data directly from the source through a data abstraction form in the nine health facilities throughout the project period. Further, the community health workers and volunteers will also provide information of the number of cases they refer to specific facilities. Cases that fail to arrive at the health facilities will also be captured and the data from the facilities and the community health workers will be cleaned, cross checked and analyzed to provide required results for utilization of neonatal services.

Quality of care will be determined through observations of service provision by clinicians, as well as checking use of neonatal equipment and the severity of conditions managed by the health providers in the units.

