#### Rationale

The project will establish 7 new special care units and enhance capacity in 2. Following the 3 months module based competency based neonatology course for 90 health care workers in these units, it will be important to provide medical consultation support by pediatricians. This will facilitate timely clinical decision making including and not limited to; judicious use of medicines such as antibiotics, change of treatment, fluids administration, nutritional calculations, immunization decisions, evolution of diagnosis, need for referral and follow up strategies. This virtual support will build the clinicians confidence in clinical management of newborns, knowing that they can ask and get help at any time of the day, all week, ultimately improving outcomes.A major challenge for clinicians working in peripheral, rural areas in Kenya, has been keeping in touch with best care practices due to inability to access this information, lack of continuous education on how to apply the updates on best care and failure of follow up on adoption of best care practices. The telehealth platform will provide virtual best care practices updates service regularly and interactively. Pediatricians and the special units’ clinicians will be able to discuss on implementation of the updates, challenges they face and lessons learnt. This will promote free flow of information between the consultants and the clinicians, promoting best care practices and newborn outcomes.The telehealth platform will enable data collection on clinical challenges and gaps that will inform project evaluation, areas of emphasis in the continuous medical education and enhanced efficiencies in other processes such as call center follow up and referral systems.

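### The primary outcome is an uncontrolled before/after count of newborn deaths, while the project itself improves record-keeping and no comparable source is fixed for the earlier deaths

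*Protocol article*

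**What the plan says.** All references are to the protocol article.

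- **Primary outcome measure.** Newborn deaths at the nine project facilities during implementation are compared "with the number of deaths at the same facilities in the similar period before the intervention; converted to percentage and aggregated by facility". As worded, this is a count with no denominator and no intervention-control contrast. The Abstract describes the project as "geared towards reducing neonatal mortality rate by 30% between October 2015 and December 2018 in Bungoma County, Kenya".
- **Quantitative data (the later section of that name, describing the tools).** Of the data abstraction form it says: "This will be developed to collect routine health facility records in the neonatal unit to ensure completeness and accuracy in data generated". On who maintains the records: "The trained nurses and clinical officers will ensure correct data entry which will be monitored periodically". The monitoring is shared between the hospital and the project, and the trained staff also mentor colleagues in recording.
- **Operationalization of the telehealth platform, Rationale.** "The project will establish 7 new special care units and enhance capacity in 2".
- **Control group – Minimizing bias and contamination.** On measuring service utilization: "we will collect data directly from the source through a data abstraction form in the nine health facilities throughout the project period". The intervention sites will include the two hospitals that already have some neonatal facilities.
- **Study design** and **Sources of data collection.** Data collection before and after the intervention is planned, and routine facility data and a baseline survey are listed as sources. Neither section says which record supplies the deaths in the earlier period.

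**The concern.** The earlier deaths were recorded before the form, the training, the monitoring and the mentoring existed. The later deaths are recorded under all four. Those measures are meant to make records more complete, so a death of the same kind may be more likely to be counted after the start than before it. The outcome is a simple ratio of two counts at the same hospitals, so nothing in it separates a change in recording from a change in mortality.

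The new units add to this. The one abstraction tool described draws on neonatal-unit records, and in seven of nine hospitals the unit is set up by the project. If the later deaths were taken from unit records and the earlier ones from elsewhere, the two counts would come from different sources.

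What is at stake is the reading of the 30% target. A missed target could not be told apart from better record-keeping.

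**Working it through.** **No plan figure to reproduce.** The 30% is a target, not a derived quantity, and the documents give no completeness of death recording for either period.

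**Formula.** Let *d* be the true proportional reduction in deaths, and let *c0* and *c1* be the shares of deaths recorded before and after. Then

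observed reduction = 1 − (1 − *d*) × *c1*/*c0*.

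**Inputs.** *d* = 0.30 is the project's target (Abstract). *c1* = 0.95 and *c0* from 0.90 down to 0.60 are assumptions for illustration only.

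| *c0* (assumed) | 0.70 × 0.95/*c0* | Observed change |
|---|---|---|
| 0.95 | 0.700 | 30% fall (no distortion) |
| 0.90 | 0.739 | 26% fall |
| 0.80 | 0.831 | 17% fall |
| 0.70 | 0.950 | 5% fall |
| 0.60 | 1.108 | 11% rise |

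**Break-even.** A true 30% fall disappears when *c1*/*c0* = 1/0.70 = 1.43, for example when recording goes from 70% to 100%.

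**No true effect.** If recording goes from 80% to 95%, then 0.95/0.80 = 1.19, an apparent rise of about 19%.

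**Would a control contrast help?** In a ratio of the two groups' before/after ratios, the recording factor becomes (*c1*/*c0* in intervention hospitals) divided by (*c1*/*c0* in control hospitals).

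- Training is listed under Study design as cross-cutting, and Table 1 bases the 90 trainees in nine hospitals. That part of the change is shared and tends to cancel.
- The units are not shared in the first year. If both hospitals with existing facilities are intervention sites, 5 − 2 = 3 new units start there, while all 4 control hospitals wait until after year 1 (3 + 4 = 7). Any recording change that comes with a new unit would not cancel.

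A concurrent contrast would therefore offset part of the distortion. The primary outcome as defined uses none.

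**The case against.** The strongest reply is that the article does not restrict the deaths in the way a reader might infer. One could read the abstraction as covering only the project period and only the neonatal unit, so that seven hospitals would have almost no earlier deaths and an undefined percentage. The documents do not support that reading:

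- The sentence about abstraction throughout the project concerns utilization, not deaths.
- Pre-intervention and routine facility data are foreseen.
- The primary outcome counts deaths at the facilities, not in their newborn units, and the form is never named as the source of deaths.
- Study design speaks of refurbishing newborn units at the experimental hospitals, so the absence of any earlier unit record is an inference.

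Three further objections have weight. Training reaches control hospitals too, so a concurrent contrast would remove some of the recording change. More complete recording works against the project and cannot by itself produce a false success; staff recording an outcome of their own work could push the other way, so the net direction is not established. The completeness values are assumed.

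These points narrow the concern but do not remove it. The primary outcome still has no control contrast, recording is still meant to improve during implementation, and the article states no common source for the two periods. Nor is this a detail that an analysis plan could settle later, because it could not restore completeness that nobody measured.

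**Conclusion.** The concern holds in a limited form. The article itself states both the planned improvement in recording and the uncontrolled before/after count that this improvement would distort. The one abstraction tool described is tied to neonatal-unit records, seven of the nine units are new, and nothing stated makes the earlier deaths come from a comparable source.

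More complete recording after the start would, taken alone, understate a true reduction. How far depends only on *c1*/*c0*, which the documents do not give. The range shown, from a 26% fall to an 11% rise for a true 30% fall, illustrates sensitivity and does not estimate the bias in this project. The documents do not support the conclusion that earlier deaths will be missing from seven hospitals or that the percentage cannot be calculated.

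**What to change.** 1. Define the numerator as all newborn deaths in each hospital, taken from registers that existed in both periods: maternity and ward registers, plus the newborn unit where one was present.
2. Abstract the earlier period retrospectively in all nine hospitals with the same form and rules, together with births and admissions.
3. Report register completeness by hospital and period, for example months of register present and missing outcome fields.
4. Re-abstraction cannot recover deaths that were never written down. Add a sensitivity analysis over plausible values of *c0*, using the formula above.
5. Report the concurrent intervention-control contrast for the first year, before control hospitals receive their units. It offsets the part of the recording change that both groups share. Because control hospitals also receive the cross-cutting components, it speaks to the equipped units and not to the whole project.

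**Cost.** Extra abstraction work on existing registers with a form already planned, and no new patients or procedures. The numerator is limited to sources available in both periods, so some deaths captured only by the new units may be left out of the primary count.

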### Qualitative

#### Tools

Provider observed interviews – observation of neonatal care services will be conducted to determine the quality of care provided by cliniciansIn-depth Interviews- for key informants to check on policies and practices surrounding new born health services. It will include policy of deployment of personnel to various units, performance assessment of personnel, availability of drugs and supplies.15 score -Severity of illness of the babies admitted in specialized neonatal units in the project sites.

### Operationalization of the telehealth platform

#### Brief description

The telehealth platform will provide a virtual consultation support environment for the clinicians in the special care units and pediatricians on call. Additionally, it will be used for continuous medical education and mentorship of the clinicians.

#### Rationale

The project will establish 7 new special care units and enhance capacity in 2. Following the 3 months module based competency based neonatology course for 90 health care workers in these units, it will be important to provide medical consultation support by pediatricians. This will facilitate timely clinical decision making including and not limited to; judicious use of medicines such as antibiotics, change of treatment, fluids administration, nutritional calculations, immunization decisions, evolution of diagnosis, need for referral and follow up strategies. This virtual support will build the clinicians confidence in clinical management of newborns, knowing that they can ask and get help at any time of the day, all week, ultimately improving outcomes.A major challenge for clinicians working in peripheral, rural areas in Kenya, has been keeping in touch with best care practices due to inability to access this information, lack of continuous education on how to apply the updates on best care and failure of follow up on adoption of best care practices. The telehealth platform will provide virtual best care practices updates service regularly and interactively. Pediatricians and the special units’ clinicians will be able to discuss on implementation of the updates, challenges they face and lessons learnt. This will promote free flow of information between the consultants and the clinicians, promoting best care practices and newborn outcomes.The telehealth platform will enable data collection on clinical challenges and gaps that will inform project evaluation, areas of emphasis in the continuous medical education and enhanced efficiencies in other processes such as call center follow up and referral systems.

#### Operation

The telehealth platform is a virtual support system. Clinicians and pediatricians will be supplied with smart phones with a telehealth application and internet accessibility. For consultations, the special care units’ clinicians will be able to post patient data such as clinical history, examination findings, laboratory results, imaging data, treatment and evolution of clinical status. The pediatrician on call will then provide the necessary professional advice. The consultation will be tracked to conclusion and archived for analysis. Servers will be housed at Mount Kenya University, main campus, Thika, Kenya and the IT support services provided by developer and the department of IT. Best care practices will be posted by project lead and pediatrician regularly.

#### Inputs

Smart phonesComputersTelehealth standard operating proceduresTelehealth softwareInternet chargesServers and maintenance

#### Outputs

Telehealth consultation dataNumber of beneficiaries and outcomesPostings of best care practice guidelinesDiscussion forum dataLessons learnt

### Beneficiaries

Newborns and their mothers.

### Operationalization of the call center service

#### Brief description

The call center service will link between the special care units and the community based midwifes and mothers of newborns. It will provide information to mothers in supporting their ability to make decisions on wellness of the newborns in the community and health seeking decisions such as urgency of taking their babies to hospital and which facility will be most appropriate. Besides, it will be used as a follow up strategy after discharge. Additionally, the service will post messages promoting newborn health for use by mothers and women on antenatal clinic follow up. Ultimately, the call center will facilitate development of a community referral system for newborns, improve mothers of newborns health knowledge, timely decision making and outcomes.

#### Rationale

More than 50% of neonates in Bungoma County are delivered without skilled attendance, in below par hygiene environments such as home and on the roadsides. This exposes the newborns to risk of infection among other complications. Often, these newborns fall ill and delay in seeking health services worsens outcomes. The call centre service, aims to streamline community based referral system, whereby, community based midwifes will report all deliveries in their locations to the call centre and the newborn mothers will be contacted and enrolled for follow up and provided with information to be able to make timely decisions for health seeking besides being sensitised on the availability of the special care units services near them.Newborn follow up after discharge is a critical component of care in sustaining wellness beyond the first month of life. A significant number of mothers may not be able to detect early symptoms of newborn illness such as sepsis or jaundice. The call centre service will actively prompt mothers on follow up after discharge to check out on symptoms and advise accordingly.Women on antenatal care follow up need information on how to nurture their newborns after delivery. Nonetheless, it has been noted that ante natal clinic attendance varies widely with drastic falls between second, third and fourth visits. Besides, since most of the health education sessions are held in the morning, mothers coming late do not attend and lose out on the education. This service will augment the ante natal care clinics in providing this information using calls and text messaging in addition to encouraging clinic attendance. The high mobile telephony penetration in the county makes this service feasible.The call centre service will provide a link between the community and the telehealth platform by providing community derived data that will inform project monitoring, strategies to enhance efficiencies in processes such as referral systems, community based midwifes engagements and newborn follow up outcomes.

#### Operation-how the call center service will work

In order to support newborns’ mothers on checking on their babies’ health through follow up, we plan to use the following strategies:

For mothers who are able to read and write an sms, the call center attendant will send out an sms 3 times a week in the mothers best language of comprehension (e.g. Kiswahili, Kibukusu, Kisabaot etc.) prompting them to check and feedback on the following:Ability of the newborn to breastfeedSymptoms of dehydrationIrritabilityBreathing- ease or difficultyHotness or ‘coldness’ of body2.For mothers who are not able to read or write an sms, the call center attendant will make a call 3 times a week in the mother’s best language of comprehension prompting on the above a-e.3.In case responses following the above enquiries are not satisfactory (or point to a baby having a health problem) they shall be advised on immediate measures to take and referred to the special care units.4.Mothers will be able to initiate the sms or call in case they need any help or information.5.Immunization information will also be provided.6.Expectant mothers will be called or texted with messages promoting knowledge on newborn health such as exclusive breastfeeding, immunization, hygiene and danger symptoms.

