### Sample size determination

#### Selection of community members (newborn mothers)

Bungoma County, the area targeted by community sensitization will be source area for target newborn caregivers/newborn mothers who will be simple randomly selected to participate in the survey. Statistical methods for determining sample size will be employed to ensure the correct sample size is picked to avoid biases and ensure the outcomes are valid. There are approximately 29,845 births in Bungoma County per annum [16]. This number will be split twice for control and intervention group. The study will allow a margin of error of 5% at confidence level of 95% to obtain the correct sample size for the study. It is also expected that at least one of the variables of interest (e.g., knowledge of 3 danger signs in neonates) will be 50% among the respondents. Using the formula:$$ x=Z{\left({}^c{/}_{100}\right)}^2r\left(100-r\right) $$$$ n{=}^{N\ x}{{/_{\Big(\left(N-1\right)E}}^2}_{+x\Big)} $$$$ E=\mathrm{Sqrt}\left[{}^{\left(N-n\right)x}{/}_{n\left(N-1\right)}\right] $$where *N* is the population size, *r* is the fraction of responses that we are interested in, and *Z*(*c*/100) is the critical value for the confidence level *c*, we get 375 as our ideal sample size in the control and intervention areas (i.e., four data collectors in each area conducting 8 surveys daily for 12 working days each). See Additional file 1.

**Table 1 Tab1:** Outcomes and objectives

Outcomes	• Increased access and utilization of quality neonatal care services. • Health system management strengthened to deliver quality neonatal health services.
Objectives	i) To setup 7 differentiated neonatal special care units in 7 sub-county hospitals in Bungoma. ii) To train 90 selected health workers (nurses and clinicians) based in 9 sub county hospitals in neonatal care to be able to diagnose and manage common new-born problems and make timely referral when appropriate. iii) Establishing a tele-health platform that will ease diagnostic and new-born clinical care consultant support iv) Re-packaging and distribution of best-practice clinical guidelines into user friendly formats. v) Develop a mobile phone based follow up system for all new-borns for early detection of neonatal problems and initiation of appropriate action.

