#### Outputs

Number of callsNumber of referralsCommunity events based surveillance data fed into the telehealth platformNumber of newborns followed up.Number of expectant mothers followed up and messaged

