#### Interphase of telehealth platform and call center

The two innovations, telehealth and call center are key components in the success of the project. These will interphase as follows;The call center will promote community referral system linkage with the community based midwifes and the special care units, promoting utilization of the units. The telehealth platform will enhance the capacity of the clinicians in these units raising standards of care, user satisfaction and ultimately improving neonatal health outcomes.The call center will focus on follow up of the neonates born within the county health care system and without. The follow up data will be uploaded into the telehealth platform allowing the project pediatricians and clinicians understand the situation of the newborns in the community, respond to queries arising during follow up and streamline care and discharge processes in the special care units. See Fig. 1.

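### The primary outcome is named for the county but counts deaths at nine facilities only, and the call-centre contacts that could supply day-28 vital status are not used for it

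*Protocol article*

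**What the plan says.** **Outcome.** The section Primary outcome measure gives the outcome as "Percentage reduction in newborn deaths in Bungoma County between October 2015 and December 2018". The next sentence defines the measurement: deaths at the nine project facilities during implementation against deaths at the same facilities in a similar earlier period. None of the five outcomes under Secondary outcome measures concerns death. The last of them (outcome e in the abstract) is the percentage of admitted neonates staying beyond 5 days.

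**Call centre.** According to the Rationale for the call centre, community midwives report all deliveries in their locations and the mothers are then enrolled for follow-up. The section on the interphase with telehealth says that follow-up covers babies born inside and outside the county health system. Contact is frequent: "the call center attendant will send out an sms 3 times a week in the mothers best language of comprehension", or for mothers who cannot read or write, "the call center attendant will make a call 3 times a week in the mother’s best language of comprehension". The prompts cover five signs: breastfeeding, dehydration, irritability, breathing and body temperature. Advice and referral follow "In case responses following the above enquiries are not satisfactory (or point to a baby having a health problem".

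**Data from the call centre.** The listed outputs start with "Number of callsNumber of referralsCommunity events based surveillance data fed into the telehealth platformNumber of newborns followed up" and end with expectant mothers followed up. The Rationale mentions "community based midwifes engagements and newborn follow up outcomes" among the community data, and the interphase section adds "The follow up data will be uploaded into the telehealth platform". Neither says whether survival is recorded, and neither is tied to an outcome. Objective v in Table 1 is: "Develop a mobile phone based follow up system for all new-borns for early detection of neonatal problems and initiation of appropriate action".

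**The concern.** The label and the measurement cover different populations. According to Selection of hospitals for the study, the county has 177 health facilities. Nine are in the project, so deaths in the other 168 are not counted, nor are deaths at home or in transit.

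A partial count need not be misleading. If the share of deaths outside the nine facilities stayed constant, the percentage change in the facility count would equal the county change. This project sets out to change that share. It builds newborn units, sensitises communities, refers through the call centre, and aims to raise the proportion of babies with complications who present from 21% to 32%. A baby who would have died at home and now dies in a newborn unit adds one death to the primary outcome and none to the county total. Conversely, a baby discharged who then dies at home leaves the facility count unchanged and appears in no outcome.

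At stake is whether the reported percentage can be read as the county effect. The same problem touches the year-1 comparison, because the new units open first in the intervention sites and a shift in place of death would be expected to differ between the two groups of sites.

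**Working it through.** The plan gives no figure for this point, so there is none to reproduce. The arithmetic below shows scale and direction.

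**Inputs from the protocol article**
- Births per year: 29,845 (Selection of community members).
- Neonatal mortality: 31 per 1000 live births (Background).
- Target: a 30% reduction (Abstract).
- Babies with complications who present: 21%, to be raised to 32% (Selection of participants for the clinical observations).

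**Inputs not in the documents, therefore assumed**
- *o*, the share of neonatal deaths outside the nine facilities at the start: 20% to 65%. The figure of more than 50% of births without skilled attendance and the 21% who present suggest that it is not small, but neither is a place of death.
- *s*, the share of the remaining outside deaths that move into the facilities.

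**Step 1, scale.** 29,845 × 0.031 = 925 expected neonatal deaths a year. The target is 0.30 × 925 = 278 a year. Deaths outside the count would be 925 × *o*: 185, 324, 463 or 601 a year at *o* = 20%, 35%, 50% or 65%. These are levels, not biases.

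**Step 2, effect of a shift.** Let deaths fall by 30% in both settings, so the true county change is -30%. Then

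facility change = 0.7 × [1 + *s* × *o* / (1 - *o*)] - 1.

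With *s* = 0 this is -30% whatever *o* is. One value of *s* can be derived from the plan's own target. If presentation rises from 21% to 32%, non-presentation falls from 79% to 68%, so 11/79 = 13.9% of those who did not present now do. Applying this to deaths is an assumption.

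| *o* | *s* = 10% | *s* = 13.9% | *s* = 25% | *s* = 50% |
|---|---|---|---|---|
| 20% | -28.3% | -27.6% | -25.6% | -21.3% |
| 35% | -26.2% | -24.8% | -20.6% | -11.2% |
| 50% | -23.0% | -20.3% | -12.5% | +5.0% |
| 65% | -17.0% | -11.9% | +2.5% | +35.0% |

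Worked cell: *o* = 50%, *s* = 25% gives 0.7 × (1 + 0.25 × 1) - 1 = -12.5%.

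**Step 3, the other direction.** If deaths move out of the facilities, for example to after discharge, the facility count falls with no change in the county. The documents do not show which shift would dominate.

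**Step 4, is there another mortality source?** The five call-centre prompts do not ask about survival. The outputs name no deaths. The follow-up outcomes and surveillance data are not defined. The section on minimizing bias and contamination says that referred cases who do not arrive are captured, but for measuring utilization. No section feeds any of these into a mortality outcome.

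**The case against.** **Follow-up data may already include deaths.** The article names follow-up outcomes and community surveillance data without defining them, and an article need not list every field. This stands as far as it goes: survival may be recorded. It does not change the outcome definition, which is stated and confined to the nine facilities.

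**The call centre is an intervention component, not a measurement system.** This also stands. The gap arises from the outcome definition. If every mother answered every message, the primary outcome as written would be the same. The call centre matters here because it offers a cheap way to narrow the gap.

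**A partial count can still give the right percentage.** True if the share of deaths outside is stable. The project's own target of more presentations argues against stability.

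**A stronger reading is tempting.** A reader might infer that, because action is tied to an unsatisfactory response, a baby whose mother stops answering is handled as well, that this is why home deaths go uncounted, and that it contradicts the Table 1 objective of following all newborns. The documents do not support this. The text is silent on non-response. The call-centre Inputs list a manual of operation that is not shown, where such a rule would normally sit. Prompts recur three times a week, mothers can start contact themselves, and referred cases who do not arrive are captured. Nor can an early discharge followed by death be said to score as a success on outcome e, since the article does not say which direction of that outcome is favourable.

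**Conclusion.** The point holds in this form: the primary outcome carries a county label but counts deaths at nine facilities, in a project designed to change where sick newborns are seen. Read as a county effect, the result can be wrong in either direction. No existing outcome would reveal this, although the project plans repeated contact with newborns' families inside and outside the health system.

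The size cannot be fixed from the documents. With a true 30% fall everywhere, the facility change lies between -27.6% and -11.9% if the shift matches the plan's presentation target. At a shift of 25% it lies between -25.6% and +2.5%. Both ranges rest on an assumed outside share of 20% to 65%, an assumed shift, and an equal true fall in both settings. The annual number of uncounted deaths gives scale only and should not be cited as the bias.

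This is an improvement worth making. It does not show that the facility comparison is invalid as a facility comparison.

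**What to change.** 1. Add one vital-status item at day 28 to the existing contacts: alive, died (with date and place), or unknown. Record non-contact as unknown, not as alive.
2. Report day-28 deaths per 1000 enrolled newborns by catchment, with the proportion unknown, beside the facility count. Report deaths after discharge beside outcome e.
3. In Primary outcome measure, limit the conclusion to deaths at the nine facilities unless community deaths are included.
4. Ask the project to reconcile the call-centre operating section with objective v in Table 1 on how unanswered contacts are handled. That operating rule is the project's to set.

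**Cost.** One field and one question in a schedule already planned, plus the effort of limiting the unknowns, which cannot be estimated because the documents give no response rate.

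**Limits.** No such data exist before the project, so the measure serves the year-1 intervention-control comparison and trends within the project, not the before-after contrast. Its denominator is enrolled newborns, and enrolment may be incomplete. A high or unequal proportion unknown would weaken it, which is why that proportion must be reported with it.
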